# **Safety considerations**

Safety of research participants will be ensured by well maintaining confidentiality of the personal information given by the participants.

# **Plan for supervision and monitoring**

The study team will make the necessary efforts to improve the validity and reliability of the study. The random sample selection process at each stage of the sampling procedure will ensure the representativeness of the study participants. The quality of the study will be assured at all stages of study design, data collection, and analysis. The questionnaire will be translated into Nepali and pre-testing will be done in 10% of the study sample to see the flow and wording of the questionnaire. Following points will be considered to assure data quality:

**Design phase**

- A detailed search of the relevant literature of the previously published documents will be done. Qualified and well-experienced faculty members have been proposed and enumerators for this study will be the students of final year Bachelor in Public Health and they will be also trained for conducting the study.

**Data collation phase**

- Firstly, thesis writing students will be trained for data collection procedure, participants’ selection and randomization. The manual of data collection will be developed and distributed to the enumerators and study team members. Conduct a week-long training workshop to the data enumerators and dietitian regarding data collection techniques and diet counseling. The study questionnaire, anthropometric instruments, biochemical instruments will be pre-tested. Pre-testing should be conducted in order to maintain the accuracy and clarity of tools.
- Nutritional counseling and diet plan guidelines will be pre-tested in another hospital not included in the study area. Pre-tested guidelines will be approved by a multi-disciplinary expert team.
- After pre-testing all the ambiguous, misleading and wrongly interpreted questions will be omitted and the questionnaire will be revised in accordance with the findings of pre-testing. Instruments such as biochemical tools and clinical tools will be regularly calibrated before use.
- Supervision and monitoring during the data collection will be done by the investigators.
- Confidentiality while taking the interview will be maintained in order to avoid bias.
- The core study team will be made responsible to maintain the appropriateness of sampling and data collection techniques. Interviews will be conducted into the local language and the responses will be coded simultaneously on the questionnaire. The filled-in questionnaire will be checked and edited each day by the supervisor at the data collection sites.
- The data collection will be carried out in close supervision of the research team. In order to maintain the quality of the data collection, the investigators will make at least 10% accompaniments and 20% back checks every day. Any error in data collection will be recorded in the investigator logbook and the enumerators will be informed of the errors and suggested the improvement measures.
- All the filled-up questionnaires will be safely stored in a locker.

# **Expected outcome of the research**

The results of this study are expected to show that the dietitian-led dietary approach to the management of diabetes will improve on HbA1c level, nutrition knowledge score and macronutrient intake level compared to usual care among type 2 diabetes mellitus patient in tertiary care hospital in Nepal.

# **Plan for dissemination of research results**

The findings of this study will be disseminated to the national and international scientific community, stakeholders and policymakers. The final report submitted will be submitted to the University Grant Commission (UGC). The results of this study will be also dissimilated through the scientific workshops, national and international conferences and published scientific papers in peer-reviewed index journals.

# **Plan for utilization of the research finding**

The proposed study is expected to deploy two final year students who will be writing their thesis for the partial fulfillment of Bachelor in Public Health course at Asian College for Advance Studies, Purbanchal University. The students who are expected to involve in this study are currently studying Bachelor in Public Health course at Asian College for Advance Studies under Purbanchal University. These students are supposed to conduct individual thesis for the partial fulfillment of the Bachelor in Public Health Course. As a part of this study, one will be conducting research entitled “Effectiveness of IEC materials on nutrition education and counseling for diabetes patients in Tertiary care hospital in Kathmandu”. Similarly, another student will be conducting research entitled “Dietary adherence, physical activity and nutritional status of diabetes patients in Tertiary care hospital in Kathmandu”.

During this study process, they will have opportunity to enhance their research capabilities on study design, sampling strategy, data collection techniques, development of nutrition education and counselling module, data management and analysis, drafting the report and dissemination of the study results in national and international conferences and publish research article in peer-reviewed index journal.

Furthermore, this study shed light on the role of dietitians in the management of diabetes. These study findings are also expected to inform others who want to management of diabetes by nutrition education, counseling, and healthy diets.

# **Work plan**

| **Gantt chart** | | | | | | | | | | | | | | | |
| --- | --- | --- | --- | --- | --- | --- | --- | --- | --- | --- | --- | --- | --- | --- | --- |
| S.N | Activities | **2019 A.D** | | **2020 A.D.** | | | **2021 AD** | | | | | | | | |
|  |  | **Nov** | **Dec** |  | | | **Jan** | **Feb** | **March** | **April** | **May** | **June** | **July** | **Sept** | **Oct** |
| 1 | Drafting proposal | **×** |  |  |  |  |  |  |  |  |  |  |  |  |  |
| 2 | Proposal submitted to UGC and under review |  | **×** | **×** | **×** |  |  |  |  |  |  |  |  |  |  |
| 3 | Submission and approve proposal to NHRC |  |  |  | **×** | **×** |  |  |  |  |  |  |  |  |  |
| 4 | Tools development |  |  |  |  | **×** |  |  |  |  |  |  |  |  |  |
| 5 | Nutrition counselling and diet plan guidelines developed. |  |  |  |  |  | **×** |  |  |  |  |  |  |  |  |
| 6 | Orientation to stakeholders  And guidelines approval |  |  |  |  |  | **×** |  |  |  |  |  |  |  |  |
| 7 | Training of thesis writing students |  |  |  |  |  | **×** |  |  |  |  |  |  |  |  |
| 8 | Sampling framework |  |  |  |  |  |  | **×** |  |  |  |  |  |  |  |
| 9 | Finalization of intervention and usual care arms in target hospital |  |  |  |  |  |  | **×** |  |  |  |  |  |  |  |
| 10 | Tools pre-testing and finalization |  |  |  |  |  |  | **×** |  |  |  |  |  |  |  |
| 11 | Finalization of research participants |  |  |  |  |  |  |  | **×** |  |  |  |  |  |  |
|  | Baseline data collection |  |  |  |  |  |  |  |  | **×** |  |  |  |  |  |
| 12 | Intervention |  |  |  |  |  |  |  |  |  | **×** | **×** | **×** |  |  |
| 13 | Midline data collection |  |  |  |  |  |  |  |  |  | **×** | **×** | **×** |  |  |
| 14 | Midline data analysis |  |  |  |  |  |  |  |  |  |  |  | **×** |  |  |
| 15 | Endline data collection |  |  |  |  |  |  |  |  |  |  |  | **×** |  |  |
| 16 | Endline data analysis |  |  |  |  |  |  |  |  |  |  |  | **×** |  |  |
| 17 | Literature review |  |  |  |  |  |  |  |  |  |  |  |  | **×** |  |
| 18 | Report writing |  |  |  |  |  |  |  |  |  |  |  |  |  | **×** |
| 19 | Dissemination of report |  |  |  |  |  |  |  |  |  |  |  |  |  | **×** |

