# **Project summary (~250 words)**

Diabetes mellitus is one of the major intractable public health problems in developing countries including Nepal. The dietary approach is of paramount significance in the management of type 2 diabetes. There is still a lack of evidence on a dietitian-led dietary approach to the management of T2DM patients in the Nepalese context. The aims of this study is to examine the effectiveness of dietitian-led dietary approach to management of diabetes on reduction of HbA1c level, nutrition education score and macronutrient intake among T2DM patients in a tertiary care hospital in Kathmandu, Nepal.

The Dietary Approach to the Management of Diabetes (DIAM-D) trial is a hospital-based, open-label, two-armed, randomized control trial. A total of 156 participants with T2DM having HbA1c >6.5% will be enrolled in the study. Participants will be consecutively enrolled and assigned to receive nutrition education and counseling (NEC) and diet plan in the intervention group (n=78) and usual routine care in the control group (n=78) randomly. The NEC will be provided to participants on group session and the diet plan will be face-to-face individual basis at the time of enrollment and follow-ups will be done every month. Baseline data will be collected using a structured questionnaire for an interview and the biochemical tests will be measured. Baseline data will be collected at the time of enrollment, midline in three months and end-line data collection in 6 months. The primary outcome of the study will be a difference in mean change (from baseline, midline to 6 months) in the HbA1c level between the two study arms from baseline to end line. The secondary outcomes measure will be changed in biochemical and clinical parameters between the two arms at baseline midline to six months. Data will be entered using Epidata Software and transferred to the STATA/MP version 14.1 for further analysis. Data will be analyzed using an intention-to-treat basis. Independent sampele t-test will be used to estimates changes between the intervention and usual care arms.

**Key word:** Dietitian, Dietary approach, Management, Diabetes, Nepal

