**Independent variables**

- - **Socio-demographic information (from Baseline):** Age, Sex, Education level, Occupation, Religion, Marital status, Residence, Smoking habit, and Alcohol habit
  - **Clinical and biochemical parameters (baseline end line):** HbA1c, fasting blood glucose, Systolic diastolic blood pressure, Lipid profile, Quality of life, Body mass index (BMI), Waist hip ratio (WHR), Physical activity level, Current medication used
  - **Dietary intake (baseline end line):** Carbohydrate, Fat, Protein, Food groups, Nutritional knowledge score on diabetes.

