## **7.9. Expected time and duration of the study**

The study will be carried out for six months, from baseline data collection, follow-up midline data collection and end-line data collection for outcome measure.

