**Tools and procedure**

- Screening checklist: This checklist entails information regarding inclusion and exclusion criteria.
- Baseline questionnaire: The study participants’ information on Socio-demographic, such as age, sex, occupation, educational level, residence, religion, ethnicity, etc. will be taken by using a face-to-face structured questionnaire interview. The questionnaire will be adopted from NDHS 2017 and STEP Survey 2019^22,23^.
- Dietary intake: Dietary intake assessment will be assessed before intervention (baseline) and after intervention (end line) using 24-hour qualitative dietary recall and food frequency questionnaire (FFQ) to compute the macronutrient intake level.
- Biochemical measurements: A fasting blood sample for HbA1c, fasting glucose, liver function test (bilirubin, ALT, AST ALP, and albumin) and lipid profile (total cholesterol, triglycerides, HDL, LDL) will be measured at baselines, three months and six months. All blood samples will be taken and handled, analyzed and disposed of according to local practice policy.
- Quality of life: The Problem Areas in Diabetes (PAID) score^24^, a 20 items questionnaire measuring the problems related to emotions, treatment, food and social support, will be measured at baselines and 12 months.
- Physical measurement: Height will be measured using a stadiometer to the nearest 1cm. Participants' weight will be measured to the nearest 0.1kg using the Seca weighing scale. BMI will be measured calculated using the widely used formula (BMI= weight (kg)/height (m)^2^), and waist Hip Circumference (WHR) will be measured using measuring tape. Systolic and diastolic blood pressure will be measured three times after 5 minute seated rest using a sphygmomanometer and stethoscope. The trained data enumerator will be taking physical measurements according to the study manual procedures.
- Nutritional knowledge score on diabetes: The diabetes knowledge test (DKT)^25^will be used to assess the nutritional knowledge score on diabetes.
- Physical activity: The physical activity will be measured using the Global Physical activity questionnaire recommended by WHO STEPwise surveillance tools^23^.
- Monitoring checklist: This will be used as every month follow up checklist. The information on lifestyle modification such as consumption of food, physical activities, adherence, and diabetic-related minor and major complication will be sought.

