# **Budget**

| **Proposed Budget for the study** | | | | | | | **Justifications** |
| --- | --- | --- | --- | --- | --- | --- | --- |
| **S.N.** | **Description** | **Person** | **Months** | **LOE (%)** | **Rate NRs.** | **Total Amount (NRs.)** |  |
| **A** | **Personal Cost** |  |  |  |  |  |  |
| A1 | Principal Investigator | 1 | 14 | 0.3 | 2,500 | 10,500 | Since both principal investigator and Co-Investigators are full-time faculty at Asian College for Advance Studies, we have allocated minimum cost that includes minimum allowances to cover their necessary expenses. |
| A2 | Co-Investigator | 1 | 14 | 0.3 | 2,500 | 10,500 |  |
| A3 | Thesis writing students | 2 | 3 | 0.5 | 4,000 | 10,000 | This cost covers the minimum remuneration for thesis writing students who will involve in this study and work as an enumerators |
| A4 | Dietitian fee | 1 | 3 | 0.5 | 4,000 | 6,000 | Dietitian will be provided with a minimum fee for the patients counseling and diet plan to the study participants |
|  | **Sub-total** |  |  |  |  | **37,000** |  |
| **B** | **Laboratory cost** | **Person Items** | **Unit** |  | **Unit Cost** | **Total Amount** |  |
| B.1 | Bio-chemical test (testing service cost) | 156 | 2 |  | 600 | 202,800 | This cost covers the Biochemical tests charge during baseline, midline and end line. |
| B2 | Stadiometer | 2 | 1 | 1 |  |  | This equipment will be provided by Asian College For Advance Studies |
| B3 | Weighing Machine | 2 | 1 | 1 |  |  | This equipment will be provided by Asian College For Advance Studies |
| B4 | BP Set | 2 | 1 | 1 | 2,500 | 5,000 | This equipment will be provided by Asian College For Advance Studies |
|  | **Sub-total** |  |  |  |  | **207,800** |  |
| **C** | **Field Cost** | **Person** | **Days** | **Times** | **Unit Cost** | **Total Amount** |  |
| C1 | Travel cost | 2 | 72 | 1 | 100 | 14,400 | This cost is allocated for enumerator travel costs during the data collection period. |
| C2 | Daily allowances | 1 | 72 | 1 | 200 | 14,400 | Daily allowances for enumerators during the data collection period |
| C3 | Survey cost (tools pretesting) | 1 | 1 | 1 | 20,000 | 20,000 | Cost for tools pre-testing (Data collection tools, IEC materials, and menu plan sheet pre-testing ) |
|  | **Sub-total** |  |  |  |  | **48,000** |  |
| **D** | **Office cost** | **Event** | **Days** | **Times** | **Unit Cost** | **Total Amount** |  |

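### The work plan puts end-line HbA1c about 3 months after baseline, although the primary outcome is set at 6 months with a separate 3-month midline

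*Protocol*

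**What the plan says.** The methods text is consistent on timing. The Project summary defines the primary outcome as the "difference in mean change (from baseline, midline to 6 months) in the HbA1c level between the two study arms" and places the assessments at enrolment, then "midline in three months and end-line data collection in 6 months". Section 7.9 gives the same length: "The study will be carried out for six months, from baseline data collection, follow-up midline data collection and end-line data collection". Section 7.10 (Tools and procedure) says that the fasting blood tests, HbA1c among them, "will be measured at baselines, three months and six months".

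The Work plan gives a different calendar. Baseline collection is marked in April 2021 only. The intervention and midline collection are each marked in May, June and July. The row "Endline data collection" is marked in July only, and so are midline analysis and end-line analysis. October holds only report writing and dissemination.

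In the Budget, laboratory line B.1 lists 156 persons, 2 units, a unit cost of NRs 600 and a total of NRs 202,800. Its justification reads: "This cost covers the Biochemical tests charge during baseline, midline and end line".

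**The concern.** The chart is the protocol's only calendar for data collection. It shows when blood is to be drawn and when the end-line data are to be analysed. If staff work to it, the HbA1c labelled as the 6-month value will be drawn about 3 months after baseline, and midline and end line can no longer be told apart. The trial would then report a roughly 3-month effect under a 6-month label. Analysis cannot repair this, because a sample that was never taken at 6 months cannot be recovered. The protocol does not say which schedule prevails where the two differ.

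**Working it through.** **Inputs**

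| Item | Methods (Project summary, 7.9, 7.10) | Work plan |
| --- | --- | --- |
| Baseline | at enrolment | April 2021 |
| Intervention | not separately dated; study lasts 6 months | May to July 2021 |
| Midline | 3 months | May to July 2021 |
| End line | 6 months | July 2021 |
| Midline and end-line analysis | not dated | July 2021 |

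The months come from counting cells in each row against the 14 month columns of the chart header (Nov and Dec 2019, three unlabelled 2020 columns, then Jan to July, Sept and Oct 2021). Every row checked has 14 month cells, so the marks are not displaced by a broken table.

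**Step 1: time from baseline to end line on the chart** (days divided by 30.44 per month)

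- Shortest, 30 April to 1 July: 62 days, 2.0 months.
- Mid-month to mid-month, 15 April to 15 July: 91 days, 3.0 months.
- Longest, 1 April to 31 July: 121 days, 4.0 months.
- The chart has no August column. If July is assumed to run on to 31 August, the longest gap is 1 April to 31 August: 152 days, 5.0 months.

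The methods' figure of 6 months is not reproduced on any of these readings.

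**Step 2: where the methods' time points would fall for an April baseline**

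- Midline at 3 months: 1 July to 30 July 2021, the month in which the chart places end line. The chart opens midline collection in May, about 1 month after baseline.
- End line at 6 months: 1 October to 30 October 2021, when the chart has no data collection.

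**Step 3: laboratory line B.1** (persons x units x unit cost)

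- As listed: 156 x 2 x 600 = 187,200, against a stated 202,800. The line does not reproduce.
- Three rounds at the listed price: 156 x 3 x 600 = 280,800, which is 280,800 - 202,800 = 78,000 above the stated total.
- Factors that do give 202,800: 156 x 2 x 650, or 169 x 2 x 600, or 156 x 3 x 433.33. The total therefore cannot show which entry is wrong.

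**The case against.** The strongest defence is that a Gantt chart is administrative and does not define the endpoint. Three separate parts of the methods agree on 6 months, and none puts end line at 3. The chart also looks carelessly filled in: it omits August, leaves the 2020 columns unlabelled and puts the literature review after end-line analysis. Staff might simply let the calendar slip and draw blood at 6 months. This stands as a reason not to claim that the trial cannot deliver its primary outcome, or that a 3-month trial was intended. It does not remove the conflict, because even the most generous reading of the chart stops about a month short.

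A reader might also infer from the budget that only two laboratory rounds, or only 3 months of work, were planned. The documents do not support that.

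- The 2 in line B.1 stands under a column headed as units, and the note beside it names three rounds. The total fits neither count at the listed price.
- The dietitian and the student enumerators are entered for 3 months at 0.5 level of effort. That is paid effort and need not equal calendar follow-up.
- The budget has other slips. The student line computes to 2 x 3 x 0.5 x 4,000 = 12,000 against a stated 10,000. The field-cost lines add to 14,400 + 14,400 + 20,000 = 48,800 against a stated 48,000.

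The variable list in section 7.8, which tags the clinical and biochemical parameters with baseline and end line only, gives no dates and adds little.

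**Conclusion.** The point holds as a conflict between the Work plan and the primary outcome schedule. As charted, end line comes about 3 months after baseline (2 to 4 months, or at most about 5 if the missing August is folded into July), against 6 months in the methods. No participant would have a 6-month HbA1c on that calendar, and the 3-month midline would coincide with end line. This rests on reading the chart's marks by column and on all baseline visits falling in April 2021, as charted.

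The evidence goes no further. Since the methods consistently say 6 months, it is the calendar that is out of step; the documents give no ground for restating the primary outcome at 3 months. The laboratory line is a separate internal inconsistency and only weak support on duration. The sample size is not affected.

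**What to change.** - Redraw the Work plan to agree with the Project summary and sections 7.9 and 7.10. Schedule midline and end line at 3 and 6 months from each participant's own baseline.
- For an April 2021 baseline, place midline in July and end-line collection no earlier than October 2021. Move end-line analysis to after the last 6-month visit, and move report writing and dissemination to follow it.
- Reconcile the May-to-July intervention window with the six-month study, so that one duration is stated throughout.
- Correct line B.1 so that persons, units, unit cost and total agree and all three HbA1c rounds are funded. At the listed unit price that is NRs 280,800, or 78,000 more than stated.

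The cost is about 3 more calendar months and a revised budget line. The primary outcome, the analysis and the number of participants do not change.

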# **Ethical issues and considerations regarding human participants**

The study will be conducted as per the guidelines formulated in the Declaration of Helsinki and ethical approval from the Nepal Health Research Council before commencing the research. This study will be registered with ClinicalTrials.gov. Every document used including questionnaire, consent, and information sheet will be submitted to the Board along with the methodology, study design, and evidence. After feedback, correction and modifications will be made into a questionnaire, and consent.

We will constitute a Data Safety Management Board (DSMB) comprising of an Endocrinologist/Physician, a dietitian, and one statistician. The DSMB members will prepare a study stopping rules and will review all the possible effects reported in the study on a quarterly basis. They will examine all participants' health status like comorbidities and decide if the study should be continued or terminated. After completed a follow up of 1/3rd of the study participants, DSMB will review data and recommend continuation, modification or termination. Any important protocol modifications, such as change of eligibility criteria, outcome analysis will be thoroughly communicated with members and will obtain amendments from NHRC.

